# Treatment outcomes in palliative care: the TOPCare study. A mixed methods phase III randomised controlled trial to assess the effectiveness of a nurse-led palliative care intervention for HIV positive patients on antiretroviral therapy

**DOI:** 10.1186/1471-2334-12-288

**Published:** 2012-11-06

**Keywords:** HIV, ART, Palliative care, Africa, Evaluation

## Abstract

**Background:**

Patients with HIV/AIDS on Antiretroviral Therapy (ART) suffer from physical, psychological and spiritual problems. Despite international policy explicitly stating that a multidimensional approach such as palliative care should be delivered throughout the disease trajectory and alongside treatment, the effectiveness of this approach has not been tested in ART-experienced populations.

**Methods/design:**

This mixed methods study uses a Randomised Controlled Trial (RCT) to test the null hypothesis that receipt of palliative care in addition to standard HIV care does not affect pain compared to standard care alone. An additional qualitative component will explore the mechanism of action and participant experience. The sample size is designed to detect a statistically significant decrease in reported pain, determined by a two tailed test and a p value of ≤0.05. Recruited patients will be adults on ART for more than one month, who report significant pain or symptoms which have lasted for more than two weeks (as measured by the African Palliative Care Association (APCA) African Palliative Outcome Scale (POS)). The intervention under trial is palliative care delivered by an existing HIV facility nurse trained to a set standard. Following an initial pilot the study will be delivered in two African countries, using two parallel independent Phase III clinical RCTs. Qualitative data will be collected from semi structured interviews and documentation from clinical encounters, to explore the experience of receiving palliative care in this context.

**Discussion:**

The data provided by this study will provide evidence to inform the improvement of outcomes for people living with HIV and on ART in Africa.

ClinicalTrials.gov Identifier: NCT01608802

## Background

In 2009, the global number of people with HIV was 33.3 million (95% CI 31.4 million- 35.3 million) with the majority in sub Saharan Africa, where 22.5 million adults and children live with HIV infection [1]. Improved treatment and care programs are urgently required [2]. Despite recent treatment guideline changes, which have raised the recommended CD4 threshold for initiation of antiretroviral therapy (ART) [3] (indicating that the population of ART patients should be expected to increase), the World Health Organization (WHO) reports that the number of eligible patients receiving treatment has increased from 28% in 2008 to 36% in 2009 worldwide. Under the previous treatment guidelines, this proportion would have been 52% in 2009 [4]. This increase in the number of eligible patients will become a mounting clinical challenge.

Studies in Brazil [5], Malawi [6], USA [7], UK [8] and South Africa [9] demonstrate that people living with HIV continue to experience a significant symptom burden after ART initiation. This was clearly demonstrated by a large UK study of HIV outpatients [10], who reported physical, psychological and global distress and symptom counts which remained unaffected by treatment status, suggesting that accessing effective treatment for the virus might not be sufficient to alleviate suffering. The prevalence of symptoms and associated distress in this patient group can be caused by toxicities from the ART itself [11-13], symptoms of opportunistic infections and co-morbidities or HIV disease [7,10,14]. People with HIV report lower quality of life [6,15-17], attributed to their physical and psychological symptom burden. In Australia, patients with HIV receiving ART had a significantly higher prevalence of depression when compared with HIV negative patients recruited from the same clinics [18]. Data from a UK study confirm this, with psychological distress reported by 75% of a sample of HIV outpatients, regardless of treatment status [8]. In Sweden, although physical health status improved after ART initiation, patients reported a deterioration in emotional quality of life, associated with an increase in the number of adverse reactions they experienced [19]. In Tanzania 53% of patients attending a clinic (of whom the majority were receiving ART), had palliative care needs [20].

Palliative care is defined by the WHO [21] as an essential component of care for people living with HIV. Palliative care includes the assessment and treatment of pain and other symptoms, whether physical, psychosocial or spiritual in nature, delivered alongside treatment. Leading experts have highlighted the false dichotomy of palliative care treatment versus cure, particularly among the vulnerable poor in developing countries [22-27]. The WHO clearly identifies an urgent need for holistic palliative care integrated with treatment for those suffering from chronic diseases such as HIV. This has been reiterated by UNAIDS, which has identified the misconception that palliative care is only appropriate for patients at the end of life, and is therefore working towards the availability of palliative care for all people living with HIV [28].

The WHO public health model of palliative care, developed in 1990, integrates palliative care into all of society, from community level to expert palliative care provision and in existing healthcare structures [29]. However, the pioneering service provision attempts and advocacy for this model are hampered by a lack of experimental research, and a lack of standardised measures and protocols, which would facilitate a more robust approach to healthcare evaluation and delivery [30]. For successful implementation, the WHO public health model of palliative care needs robust evidence of effectiveness in relevant contexts.

There are wider reasons beyond patient quality of life that indicate the importance of attention to palliative care-related problems. Depression and treatment of side effects are associated with non-adherence to ART [31,32], which increases viral resistance, rebound and infectiousness [33]. A recent systematic review of palliative care-related problems at HIV diagnosis identified significant physical and psychological symptoms among newly diagnosed HIV positive patients [34]. A systematic review of the evidence for effectiveness of HIV palliative care found that it improves anxiety, pain, symptoms, and insight but that the evidence was generated almost exclusively in the pre-ART era and in high income countries [24]. There are currently no known trials of palliative care for patients with HIV on ART. This lack of evidence originating from low and middle-income countries is problematic in light of the great disease burden in these areas.

We therefore aim to inform HIV service provision by conducting a randomised controlled trial (RCT) to assess the effectiveness of palliative care for HIV outpatients on ART, and present here the protocol for the phase III RCT with a qualitative component.

## Methods/design

### Aim and objectives

#### Aim

We aim to evaluate the efficacy, in terms of reported pain of a nurse led palliative care intervention for HIV patients on ART. Nurses will receive two weeks in depth training in palliative care and support and supervision from an experienced palliative care mentor. Two trials are being conducted, one in Mombasa, a low-income setting, and one in Cape Town, a middle-income setting. In line with guidance from the Medical Research Council (MRC) on the evaluation of complex interventions, qualitative data will also be collected to complement the quantitative data and address the question of how the intervention might work [35].

#### Objectives

1. To investigate whether self-report pain and symptoms significantly improve for HIV positive patients under palliative care compared to those in standard HIV care.

2. To compare self-report adherence to ART under palliative care compared to standard HIV care.

3. To compare self-report health-related quality of life under palliative care compared to standard HIV care.

4. To compare additional multidimensional palliative care outcomes (psychological, social and spiritual wellbeing) under palliative care compared to standard HIV care.

5. To understand the process of receiving palliative care and identify any specific component which may be the most effective aspect (i.e. access to strong analgesia, multidimensional assessment, access to multidisciplinary team).

### Study design

The study will consist of two fully powered, independent phase III clinical RCT’s preceded by a pilot. Each trial will be powered and conducted in parallel to a common research design protocol, thus providing evidence of outcomes in two different settings.

Patients will be randomly allocated to standard HIV care or standard HIV care plus palliative care. The palliative care will be delivered within the existing HIV clinic, and by existing staff, using an integrated model, with the option to refer to a specialist palliative care provider for complex cases. The study has been designed with measures to minimise potential contamination. Once the study nurses have been trained in palliative care, they will only see the patients allocated to the intervention, and will not be required to work in the main clinic until completion of the trial.

The design will be longitudinal, using repeated measures. Patient-centred outcomes will be measured using quantitative questionnaires.

#### Outcomes

The primary outcome is self-reported pain after four months. The secondary outcomes are health-related quality of life; adherence to treatment; risk behaviours; and psychological morbidity and the core domains of palliative care as defined by the WHO (physical, psychological, social and spiritual well-being) as measured by the APCA African POS.

Patients will be followed up for four months and most outcomes are measured at baseline and monthly intervals, described below.

#### Control

Patients randomly allocated to the control arm will receive the usual clinical care delivered by the HIV clinic. Nurses who have had no exposure to palliative care will provide this service.

In Kenya this consists of six-monthly clinical assessments once ART has been established, with investigations and treatment for any relevant symptoms or problems. Patient may attend the clinic for medications refill only or may request more frequent appointments if they experience a problem. In South Africa, patients attend the public hospital monthly for a brief appointment to refill medications. They may present for additional appointments as necessary.

#### Intervention

Patients randomly allocated to the intervention arm will receive clinical care from a nurse who has received two weeks’ training in palliative care and ongoing clinical support and supervision from experienced palliative care providers. The palliative care trained nurse will also have the option to refer complex cases for management at a hospice.

### Minimum package of palliative care

Patients allocated to the intervention arm will receive an initial clinical assessment , followed by either one further visit or phone call within the first week, one further visit or phone call within the second week and one visit per month thereafter. The focus of the care provided will be on holistic assessment and management of physical, psychological, spiritual and social problems. This minimum package of care can be supplemented by additional clinical support as required on a case-by-case basis.

### Intervention nurse training

Training will be provided by local expert palliative care sites, and will be delivered in an intensive 2-week period, tailored to the needs of patients living with HIV who are not necessarily in advanced stages and who are currently on ART.

The training will be designed using national and international guidelines [36,37] to ensure that the nurses are prepared to address the specific palliative care dimensions and needs of those living with HIV and taking ART, with specific focus on the management of common HIV symptoms. Within these two weeks, the nurses will also gain clinical experience, working in a palliative care setting.

### Standardised assessment form

Assessment and management of multidimensional problems is a central part of palliative care. The trained nurse will use a standardised assessment form, developed by the study team drawing on tools and models used in sub Saharan Africa, to assess the domains of palliative care as defined by the WHO [21] and monitor adherence.

### Clinical support

The nurse will receive weekly clinical support from an experienced palliative care provider, where all cases will be reviewed and decisions appraised. Drugs needed for the intervention group not stocked in the study site pharmacy will be dispensed by the supporting palliative care service.

### Referral

As part of clinical support, referral to the hospice will be available for patients in the intervention arm whose needs are “complex” or apparently refractory and who require assessment or intervention from the palliative care specialist partner site. Criteria for referral will be established prior to the study launch, and recorded in the clinical documentation.

#### Sample size

We used the largest known dataset generated by the APCA African POS (detailed below) to derive expected levels of change used in the sample size calculation. The dataset consisted of baseline data from a longitudinal evaluation of care and support which recruited 1337 HIV patients in Uganda and Kenya [38]. Stata v10.0 was used for calculations.

Sample size was first calculated based on change in the pain item of the APCA African POS, as the primary outcome. A clinically significant change in an APCA African POS item is a change of 1 point so this is identified as the expected change [39]. We propose a sample size of 56 per arm to be able to demonstrate a difference between treatment conditions for pain, symptoms, and both physical and psychological dimensions of quality of life (the latter as a mediating variable in a model of adherence). The study will recruit 60 patients per arm (120 total in each country), allowing for 6% drop-out/attrition [40].

#### Settings

The two participating HIV care facilities (one in Kenya and one in South Africa) are highly experienced HIV and ART service providers, with proven longevity. The study site in Kenya is a private clinic funded by private donations in a deprived area of Mombasa. Regular appointments are made to see a nurse for a health check and ART refill, with frequency dependant on adherence, opportunistic infections and CD4. Patients have access to a physician if referred by the triaging nurse, and good access to essential medicines. The South African study site is a government-run clinic in district township, south-east of Cape Town. Patients have monthly appointments for a health check and ART refill, and have similar access to clinic physicians as in Kenya – upon nurse referral. Access to essential medicines is mostly reliable, but is hampered by economic constraints necessitating short prescriptions. In both countries, the providers of the palliative care training and support are longstanding local experts. In Kenya, training was provided by Kenyan Hospice and Palliative Care Association (KEHPCA) with support from an expert from Coast Hospice in Mombasa. In South Africa, training was provided by Hospice Palliative Care Association (HPCA) and support was provided by an expert from Helderberg Hospice.

#### Recruitment and consent

##### Screening and recruitment

Because of organisational and logistical differences between the two study sites, recruitment will be performed in a slightly different way, whilst maintaining the integrity of random sampling and respecting the logistical constraints, patient flow and unique pressures of each clinic.

In Kenya, the initial patient to be screened will be chosen randomly using the number allocated to them at registration that day, and a number selected from a random number table. Once the initial patient has been screened, patients will be screened consecutively. In South Africa patients are simply screened consecutively according to the order in which they present at the clinic.

### Inclusion/exclusion criteria

In both countries, patients included in the study must be adult patients (i.e. aged 18 years or above), with known HIV infection who have been receiving ART for more than one month.

Patients meeting these criteria will be screened by a researcher, using first two items of the APCA African POS. If they report a score of 3, 4 or 5 on either (possible 0–5 score), they will be asked whether they have been experiencing the pain or symptoms for 2 weeks or longer. Patients who answer in the affirmative will be eligible for participation. This is in order to identify those with symptoms which suggest a chronic rather than acute problem. The researcher will then outline the study content and demands and ask whether they would like to consent to participate. This process will take place every day during the data collection period, although the time of the day will vary randomly in order to collect a representative sample of the clinic population.

In Kenya, potential participants will be screened for eligibility from a list of all patients currently in the clinic, in the triage room of the comprehensive care unit, where all HIV positive patients are seen. In South Africa, all patients in the clinic are HIV positive and on ART, therefore the researcher will sit in the clinic room with the nurse and will screen each potential participant as they attend their appointment. All patients who are called to see the nurse will be screened consecutively and invited to consent if eligible.

In summary, to be eligible for participation, patients must have sufficient cognitive ability to answer the outcome tool questions using either verbal or hand responses (see data collection below), be receiving ART for at least one month (based on clinic records) and must report either pain or symptoms of 3, 4 or 5 on the APCA African POS (i.e. severe to overwhelming) for longer than two weeks. Exclusion criteria include pain and symptoms with a duration of less than 2 weeks, receiving ART for Prevention of Mother To Child Transmission (PMTCT) of HIV, or for some other reason not related to personal clinical need or if the patient does not speak either English or Kiswahili in Kenya, and English, isiXhosa or Afrikaans in South Africa.

### Consent

If eligible, the patient is taken through the information and consent sheet in a separate private space, respecting the patient flow of the clinic and the demands on patient time. Patients will have an information sheet read aloud to them, and will then be asked to sign or mark a consent form. All information and consent forms will be translated into the principal local languages. Consent using either a signature or mark will be obtained according to local custom or patient preference. All consent forms will be kept securely at the facility, and stored separately from outcome data. Each patient will be allocated a unique identifying number, kept by the researcher.

All participants will have the right to withdraw, without notice, at any point. Participants who withdraw from the intervention arm will continue to receive the intervention for the full four months. They will be asked whether they want their data to be withdrawn. If so, it will be deleted from the database and the paper copy will be destroyed. After quantitative data collection has finished, the dataset will be anonymised and from that point it will no longer be possible to identify individuals and withdraw data.

A record of the number of patients not agreeing to participate will be kept at each facility in accordance with CONSORT guidelines for the reporting of RCTs [41].

The sample for the qualitative interviews will be purposively drawn from intervention (n=20) and control patients (n=10) based on the clinical and demographic patient characteristics and results of the quantitative data collection i.e. psychological well-being. This will attempt to ensure a representative sample in terms of demographic and clinical data, and also in terms of psychological well-being and response to the intervention.

### Randomisation

Consenting patients will be administered the initial assessment and subsequently randomised to intervention or control group. This is done using block randomisation to ensure a manageable work load for the nurse delivering the intervention, with 40 per block. Each study site has been issued with three sealable pots containing 20 pieces of paper with “I” for intervention and 20 pieces of paper with “C” for control. Once a piece of paper has been blindly selected by the researcher, the patients is informed whether they are in the control or intervention group and this is recorded on a form which is kept separately from the data collection tools and records. The piece of paper is discarded and the process continues until the pot is finished, when the next pot is then used. The allocation to control or intervention is not blinded as it would be impossible to maintain this blinding when the intervention was delivered.

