### Data management and quality assurance

A researcher will be employed at each participating centre. This person will be responsible for managing recruitment, data collection and data entry. Fortnightly study team conference calls will be used to ensure that all queries are promptly resolved, attended by all members. All quantitative data will be double-entered into purpose designed EpiData databases. Discrepancies will be resolved by referring back to the original questionnaires.

Following data checking and cleaning, the data will be imported into Stata for analysis at KCL. Qualitative transcripts will be imported into NVivo (version 9) for analysis. All hard data will be stored for at least seven years in accordance with the UK Data Protection Act 1998.

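### The researcher who recruits appears also to draw unnumbered allocation slips from a pot of known 20/20 content and discard them, so concealment is not secured and the draw cannot be independently verified

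*Protocol article*

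**What the plan says.** The protocol article describes the allocation mechanism in full under Randomisation.

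- **Order of steps.** "Consenting patients will be administered the initial assessment and subsequently randomised to intervention or control group".
- **Mechanism.** Blocking is used, "with 40 per block", to keep the intervention nurse's workload manageable. Each site holds three sealable pots, each with 20 slips marked I and 20 marked C.
- **Draw.** "Once a piece of paper has been blindly selected by the researcher, the patients is informed" of the arm, which is also written on a form stored apart from the outcome records.
- **Fate of the slip.** "The piece of paper is discarded and the process continues until the pot is finished, when the next pot is then used".
- **Blinding.** Allocation is open.

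Other sections show who does this work. Under Inclusion/exclusion criteria: "Patients meeting these criteria will be screened by a researcher, using first two items of the APCA African POS", and then "The researcher will then outline the study content and demands and ask whether they would like to consent to participate". Under Data management and quality assurance: "A researcher will be employed at each participating centre", and "This person will be responsible for managing recruitment, data collection and data entry".

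The article mentions no independent holder of the pots, no witness, no numbering of slips and no central release.

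**The concern.** Allocation concealment should not depend on the integrity or memory of the person who enrols patients. Here that person appears to hold every step. They screen, explain the study, complete the baseline assessment, draw the slip, announce the arm and later collect the outcomes. They know what each pot held at the start and have seen every earlier draw, so they can work out what remains.

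Two exposures follow.

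1. **Prediction.** As a pot empties, the next arm becomes easier to guess. The way the study is presented to the next eligible patient could shift accordingly.
2. **An untraceable redraw.** A slip that is looked at and put back leaves no evidence. By then the researcher has just recorded the patient's baseline pain score.

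The primary outcome is self-reported pain at four months in an unblinded trial, so secure allocation is one of the few protections against bias still available. The Discussion expects the trial to give a clear answer on effectiveness. The steps against bias that it lists (validated and translated tools, researcher training, double data entry) do not secure the draw.

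**Working it through.** **Inputs.** From Randomisation: three pots per site, 20 I and 20 C in each, drawn without replacement, open allocation. From Sample size: 56 per arm needed, 60 per arm and 120 per country recruited, 6% attrition.

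**The plan's own figures.** 56 / (1 − 0.06) = 59.6, rounded up to 60 per arm. The pots supply 3 × 20 = 60 slips per arm and 3 × 40 = 120 per site. The two sections agree.

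**Is the drawer the recruiter?** The eligibility section has a researcher screen and invite consent. The Randomisation section has the researcher draw. The data management section has one researcher per centre, who manages recruitment and data collection. No sentence says outright that they are the same individual, but one researcher per centre leaves little room for another reading.

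**Correct guesses.** Suppose someone tracks the draws and always guesses the arm with more slips left. With m slips per arm, the expected number correct per pot is

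m + 2^(2m−1) / C(2m, m) − 1/2.

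For m = 20: 20 + 2^39 / C(40, 20) − 0.5 = 20 + 3.99 − 0.5 = 23.49 of 40, or 58.7%, against 50% if draws were unpredictable. An exact recursion over the slips remaining gives the same 23.49.

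**Where in the pot** (simulation of 50,000 pots):

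| Draws | Guessed correctly |
|---|---|
| First 10 | 52% |
| Last 10 | 70% |
| Last 5 | 77% |
| Last | 100% |

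**Draws known with certainty.** Once one arm is exhausted, the rest of the pot is known. The expected number of such draws is 2m / (m + 1) = 40 / 21 = 1.90 per pot. Over three pots this is 3 × 1.90 = 5.7, about 6 of 120 per country.

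**Draws with lopsided odds** (exact recursion, average per pot of 40):

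| Chance of the likelier arm | Draws per pot |
|---|---|
| at least 60% | 11.7 |
| at least 2/3 | 6.9 |
| at least 75% | 3.6 |

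**Redraws.** A returned slip changes which patient receives which arm, never the pot's total, so a complete pot still tallies 20/20. The check that the allocation form allows would therefore not reveal a redraw. The documents give nothing from which to estimate how often this might happen.

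**The case against.** The strongest defence is that the procedure has real safeguards. The pots are sealable and the draw is described as blind. It follows consent and the baseline assessment, and there is no list to look ahead in. In South Africa screening is consecutive. In Kenya it is consecutive after a randomly chosen first patient. The time of day varies at random, and refusals are counted. The allocation form lets the order and the 20/20 tally be checked. Early in a pot the next slip is close to a coin toss. Custody of the pots and handling of the slips may be set out in a fuller protocol that is not shown. The Analysis section also plans adjustment for baseline differences and covariates.

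Much of this stands, and it rules out stronger readings that a reader might infer:

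- **That the pot is open and allocation wholly unconcealed.** The text says otherwise, and concealment is insecure rather than absent.
- **That there is no audit trail.** The form is one. What it cannot show is that the recorded slip was the first one drawn.
- **That the recruiter freely chooses whom and when to screen.** The screening rules restrict this.
- **That redraws are unlimited in number or did occur.** The documents support no figure, and a redraw cannot alter the totals.

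What the defence does not meet is the central point. Every safeguard on the draw is carried out by the person from whom the next allocation should be concealed. Consecutive screening limits who is approached, not how the study is presented. A draw after baseline protects the baseline measurement, but it also means the drawer has just seen the pain score. Covariate adjustment deals with measured imbalance, not unmeasured.

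**Conclusion.** The procedure as written does not secure concealment, makes allocations late in each pot predictable, and leaves the draw without independent verification.

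The predictable part is modest: 59% correct guesses overall instead of 50%, with the excess mostly near the end of each pot, and about 6 of 120 patients per country whose arm is known beforehand. The larger exposure is the redraw that leaves no trace, and its size cannot be stated from the documents.

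The figures assume that the drawer tracks every earlier draw and that each pot is used to the end. The conclusion also rests on reading recruiter and drawer as the same person, which the three sections together support but do not state. Nothing here shows that allocation was in fact steered. The change should be made before further patients are randomised, because selection on unmeasured prognosis cannot be corrected in the analysis.

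**What to change.** For all patients not yet randomised, replace the pots.

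1. The coordinating centre generates a 1:1 list for each country, using permuted blocks of varying size that are not disclosed to the sites.
2. Each allocation is released by text message from the centre, or by sequentially numbered, opaque, sealed envelopes.
3. Patient ID and date are recorded after the baseline assessment and before the allocation is opened.
4. Envelopes and slips are kept and reconciled with the list.
5. If envelopes are used, an existing staff member who neither recruits nor treats patients in either arm holds and opens them. If no such person is available, use central text release.

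Block sizes must stay undisclosed. With a known fixed block of 4, the same guessing strategy would be right 71% of the time, which is worse than the present 59%. Smaller varying blocks still serve the stated aim of an even workload for the intervention nurse.

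The article says the pots have already been issued, so the change may fall mid-trial. In that case record the changeover date, count the slips left in any part-used pot against the allocation form, and report both.

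The cost is stationery or text messages, a short amendment and a few minutes per patient. No new post is needed.
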